## Abstract

**Background:**

Parental well-being can be seriously impacted during the challenging perinatal period. Most research and support services focus on perinatal psychopathology, leaving a need for programs that recognize and enhance the strengths and well-being of parents. Furthermore, fathers have received minimal attention and support relative to mothers, despite experiencing perinatal distress. New parents have limited time and energy to invest in program attendance, and web-based programs provide an ideal platform for delivering perinatal well-being programs. Such programs are globally accessible, available at any time, and can be accessed anywhere with an Internet connection.

**Objective:**

This paper describes the protocol of a randomized controlled trial investigating the effects on first-time parents’ perinatal well-being, comparing two versions of the online program Baby Steps.

**Methods:**

The clinical trial will randomize 240 primiparous mother-father couples to either (1) Babycare, an online information-only program providing tips on selected childcare issues, or (2) Well-being, an online interactive program including all content from the Babycare program, plus parental well-being-focused content with tools for goal-setting and problem solving. Both programs will be supported by short message service (SMS) texts at two, four, seven, and ten weeks to encourage continued use of the program. Primary outcomes will be measures of perinatal distress and quality of life. Secondary outcomes will be couple relationship satisfaction, parent self-efficacy, and social support. Cost-effectiveness will also be measured for each Baby Steps program.

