### Hypotheses

It is predicted that participants receiving the *Well-being* program will show lower levels of distress and a higher level of quality of life at 13 and 26 weeks post-baseline, compared to participants receiving the *Babycare* program. In addition, couple relationship satisfaction, parental self-efficacy, social support, and cost-effectiveness are predicted to be greater at 13 and 26 weeks post-baseline for participants receiving the *Well-being* program, compared to participants receiving the *Babycare* program.

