#### Follow-Up Assessments

Follow-up assessments will be at 13 and 26 weeks post-baseline. For the purposes of these assessments, couples will be treated as individual participants and emailed an individualized online survey link. To maximize retention, participants will be reminded to complete the survey via scheduled emails. If the participant has not responded within two weeks of the due date, a researcher (blind to treatment allocation) will phone the participant, establish ongoing consent from the participant, and attempt to obtain the assessment over the phone. Participants will be offered an AUD $20 gift voucher (AUD $40 per couple) for completing each follow-up assessment.

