#### Sample Size

A total of 240 couples (120 couples per group) will be recruited. A sample size of 240 will give a power of .80 for detecting a significant *Time* x *Condition interaction* (*P*<.05) over three occasions of measurement, with a small effect size of f=0.082 [50,51].

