#### Primary and Secondary Analyses

All data analyses will be based on the intention-to-treat principle [53]. Continuous outcomes (eg, measures of perinatal distress, quality of life, couple relationship satisfaction) will be analyzed using general linear mixed models, and multilevel modelling will be used for nested data, to deal with any missing data.

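### The sample size covers one test at the full .05, although two primary outcomes are named and no success rule links them

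*Protocol article*

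**What the plan says.** The Methods paragraph of the abstract states: "Primary outcomes will be measures of perinatal distress and quality of life". Study Measures assigns the EPDS to distress and the AQol-8D to quality of life.

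The Sample Size section reads "A total of 240 couples (120 couples per group) will be recruited", then "A sample size of 240 will give a power of .80 for detecting a significant" time-by-condition interaction at P<.05, "over three occasions of measurement, with a small effect size of f=0.082". This is one test at one unsplit significance level, and no outcome is named.

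The Hypotheses section predicts that participants in the Well-being arm "will show lower levels of distress and a higher level of quality of life at 13 and 26 weeks post-baseline". The two outcomes are joined by a conjunction, but the section does not say what follows if only one of them shows the effect.

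Under Primary and Secondary Analyses: "Continuous outcomes (eg, measures of perinatal distress, quality of life, couple relationship satisfaction) will be analyzed using general linear mixed models". That sentence takes primary and secondary outcomes together and gives no significance threshold.

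**The concern.** The only error rate and the only power figure in the article belong to one test, while the primary conclusion will rest on two. Whether 5% and .80 still describe that conclusion depends on a success rule that the article does not give. If one significant outcome is enough, there are two chances of a false positive. If both are needed, there are two chances of a miss. A reader of the results could not tell whether one significant primary outcome out of two confirms the hypothesis or fails it, and that choice could be made after the data are seen.

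**Working it through.** **Inputs from the article.** N = 240 couples in two equal groups; m = 3 occasions; f = 0.082; significance level .05; power .80 (all Sample Size). Two primary outcomes (abstract).

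**Assumptions, because the article gives no values.** Within-subject correlation ρ = .5; sphericity; the same f on both outcomes, with the same time pattern; between-outcome correlation r of the test contrasts, shown at 0, .5 and .7.

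**Step 1: reproduce the stated power.** For the within-between interaction, λ = f²·N·m/(1−ρ) = 0.006724 × 240 × 3 / 0.5 = 9.68, with 2 and (240−2)×2 = 476 degrees of freedom. The noncentral F distribution gives power .799, which agrees with the stated .80 for one test.

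**Step 2: success if either outcome reaches .05.** With no effect on either outcome and r = 0, the family-wise error is 1 − 0.95² = 0.0975. For r > 0, two correlated 2-df tests were simulated.

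**Step 3: success only if both reach .05.** The error cannot exceed .05. With r = 0, power is .799² = .64. For r > 0 it comes from the same simulation.

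**Step 4: each outcome at .025.** Power per outcome from the noncentral F is .712. With r = 0, power for at least one outcome is 1 − (1 − .712)² = .917. Holm has the same power for at least one rejection, because its first step tests the smaller p-value at .025.

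| r | Either at .05: error | Either at .05: power | Both at .05: power | Holm: power for at least one |
|---|---|---|---|---|
| 0 | 9.75% | .96 | .64 | .92 |
| .5 | 9.1% | .92 | .68 to .69 | .86 |
| .7 | 8.5% | .89 | .71 | .82 |

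Simulated values move by up to about .005 with the run and with the use of an F or a large-sample chi-square reference. At r = 1 the two tests coincide, and only then do 5% and .80 both carry over unchanged.

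**Step 5: what N would be needed.** On the same assumptions, .80 per outcome at .025 needs about 288 couples. A joint power of .80 at .05 needs about 312 (r = 0), 296 (r = .5) or 284 (r = .7).

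**The case against.** The strongest objection is that a rule for combining primary outcomes is ordinary content of a statistical analysis plan. That plan is not shown, and the source is a condensed article. Nothing printed contradicts a multiplicity rule set out elsewhere, and quoting power for each outcome separately is common. This stands to the extent that the missing rule is not by itself the finding. What remains is what the article does fix: a sample-size basis of one test at the whole .05, beside two declared primary outcomes.

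A second objection is that the hypothesis is worded jointly, and a requirement for both outcomes needs no adjustment of the significance level. That is a fair reading. If it is meant, the 5% is safe and the shortfall lies in the power.

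Four stronger readings are tempting, and the article does not support them.
- A reader might infer that neither the 5% nor the .80 applies. Under the either-outcome rule, power for at least one outcome is .80 or more. Under the both-outcomes rule, the error is at most 5%. Neither rule fails on both counts.
- A reader might infer that the plan tests each primary outcome at .05. The threshold appears only in the sample-size sentence, so this is an inference.
- A reader might count four primary tests, with mothers and fathers tested separately. No section plans this. Parents are assessed individually, but the multilevel modelling for nested data is compatible with one joint model.
- A reader might expect a baseline-adjusted contrast averaged over follow-ups to absorb the correction easily. That is a different test from the one powered, and its advantage depends on an effect that is constant over time, which the article does not state.

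**Conclusion.** The concern holds in this limited form. The sample size is justified for one time-by-condition test at the full .05, while two primary outcomes are named and the article does not say whether success needs one or both. If either suffices, the family-wise error is about 8.5% to 9.8%. If both are needed, the error is controlled and power is about .64 to .71, not .80.

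The error range depends on the assumed between-outcome correlation of 0.7 to 0. The power range also depends on ρ = .5, sphericity and an equal f on both outcomes; a smaller effect on either one would lower the joint power further. The unit behind the figure of 240 is not settled by the arithmetic, since 480 individuals with ρ = 0 give the same .80.

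**What to change.** State one success rule for the EPDS and AQol-8D before analysis, and restate the power for that rule. There are two workable choices.

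1. **Holm across the two tests at family-wise .05.** On the planned interaction test with 240 couples, power for at least one outcome is about .82 to .92, and .71 per outcome at .025. The cost is a stricter threshold for the smaller p-value.
2. **Both outcomes required at .05**, if the joint wording of the hypothesis is meant. No adjustment is needed. The cost is a less favourable stated power of about .64 to .71.

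Either choice takes a sentence in Primary and Secondary Analyses and a revised figure in Sample Size, with the assumed correlations given. The Results section reports that recruitment ended in October 2015, so the larger samples in the working are not a realistic remedy. The rule itself could still be fixed before the results expected in July 2016, and neither choice needs more couples.

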**Results:**

Participant recruitment commenced March, 2015 and continued until October, 2015. Follow-up data collection has commenced and will be completed May, 2016 with results expected in July, 2016.

**Conclusions:**

Perinatal distress has substantial impacts on parents and their infants, with potential to affect later childhood adjustment, relationships, and development. This study aims to test the impact of a highly accessible online program to support parental coping, and maximize the well-being of both parents. By including fathers in the program, Baby Steps has the potential to engage and support this often neglected group who can make a substantial contribution to familial well-being.

**ClinicalTrial:**

Australian & New Zealand Clinical Trials Registry: ANZCTR12614001256662; https://www.anzctr.org.au/ Trial/Registration/TrialReview.aspx?id=367277 (Archived by WebCite at http://www.webcitation.org/6ibUsjFIL)

## Introduction

The perinatal period is challenging for parents, and the changes and demands encountered during this life transition can seriously impair parents’ well-being. The impact of these challenges is well-recognized in mothers with postpartum depression rates of approximately 20% in Australian women [1]. Most new mothers (50-80%) experience some distress [2]. A meta-analysis of fathers’ postpartum mental health found comparable rates of depression (10%) [3], with Australian figures reporting the rate at approximately 5% [4,5]. Initiatives by *beyondblue* and the Federal Government have increased perinatal depression screening and intervention rates in Australia. However, screening and preventive programs for perinatal depression have not been universally available [6], and have been almost non-existent for fathers, despite the potential suitability of the Edinburgh Postnatal Depression Scale (EPDS) for fathers [7]. Lack of availability of these father-specific programs is a reflection of both supply (eg, a focus on mothers, service capacity, and staff adherence) and demand issues (eg, reluctance to disclose symptoms and receive treatment) [8]. An accessible perinatal well-being intervention designed for both mothers and fathers is the target of this trial.

Postpartum distress has significant and wide-ranging consequences. In mothers, postpartum distress affects attachment [9], child development [10], and academic achievement [11]. Some effects can be long-lasting, including increased risks of later childhood behavioral problems [12] and subsequent episodes of parental depression [13]. More recently the negative effects of paternal postpartum distress have been reported, including its association with emotional difficulties in children [14], the impact on marital relationships and family well-being [15], and the detrimental effect on the mother’s relationship with her child [16].

In addition to significant costs to family well-being, perinatal distress has high economic costs. The annual health costs associated with perinatal depression and anxiety could be up to AUD $70 million in new mothers and AUD $16 million in new fathers, if their baby was delivered in 2012 [17]. The cost of psychological distress in otherwise healthy adults is substantial. For example, lost productivity cost Australian employers AUD $5.9 billion in 2009; productivity losses for each treatment seeker were AUD $19,810 for men and AUD $9183 for women [18]. The cost from one year’s lost productivity for untreated maternal depression is AUD $142 million [17].

Many mothers prefer psychosocial treatments during the postpartum period, especially while breastfeeding [19]. Rapid acting, easily communicated treatments for depression in other contexts involve behavioral activation [20], physical activity [21], problem solving [22], parenting skills and self-efficacy [23-25], social support networks [24,26], and meditation mindfulness [27]. Treatment with a mental health professional is not easily accessible for non-urban populations, creating a barrier for treatment [28].

There is growing evidence, however, that interventions may not always require substantial clinician involvement to reduce distress. A single face-to-face psychoeducational session with a maternal and child health nurse was found to reduce depression and anxiety in women without psychiatric histories [23]. Another study found no difference in clinical outcomes between a psychoeducational booklet and group cognitive behavior therapy (CBT) in primary care [29]. In the second study, however, 60% of eligible women turned down group CBT, highlighting that traditional interventions may not match the needs of new parents. Adherence to treatment appeared especially low when symptoms were mild, women had competing commitments, or motivation was limited. Women also cited time, childcare, and transportation as further barriers to engagement.

Online interventions may overcome these uptake barriers, as the Internet is a highly accessible and cost-effective vehicle for the delivery of flexible and sustainable support. In 2012-2013, 83% of Australian households had Internet access [30], and 89% had a mobile phone with Internet access [31], indicating that electronic interventions are available to most Australians. Internet-based interventions have well-established efficacy for alleviating depression and anxiety, and for promoting well-being [32]. Clinical gains approximate those from face-to-face treatment, especially when dealing with low-severity problems [33]. In addition, stigma is avoided and location inequities are minimized.

The Internet has already proven feasible for screening postpartum depression in mothers [34]. Furthermore, randomized controlled trials (RCTs) for two online postpartum depression treatment programs found decreases in postpartum depression at 12 weeks [35] and 17 weeks [36] respectively, as compared to conventional treatment. Online treatment for postpartum depression shows promise, and may address the substantial economic, community, and family impact of perinatal distress. Development of programs that promote the maintenance and enhancement of perinatal mental well-being should be a priority.

The perinatal period is a time of transition [37], offering a window of opportunity when timely introduction of tools and information could positively influence later outcomes [38]. For example, a study investigating the well-being of 5000 mothers found that positive maternal outcomes after birth are influenced by mental and physical well-being during the perinatal period [38]. Perinatal well-being is a complicated construct determined by an individual’s perception and evaluation of their life during the perinatal period [37]. If expectant and new parents were offered tools to support and enhance well-being throughout this process, both maternal [39] and paternal [40] outcomes could be improved *.* However, few universal strategies for preventing perinatal distress and enhancing well-being have been evaluated in rigorous, large-scale studies [37].

Online programs targeting prevention of postpartum depression are in their infancy. A fully-automated program developed for pregnant women presented psychological strategies across 44 short sessions [41]. Information in this program was presented on a schedule, and this lack of flexibility may be a deterrent for some mothers. An RCT testing the effectiveness of this program is currently underway [42]. A second online prevention program has been evaluated in a pilot trial, but the study found no differences in effectiveness between the online program and the information-only control condition [43]. A limitation of this study was the minimal program use by participants, suggesting that email or text message reminders could be used to increase retention and use of the program. Furthermore, the intervention was linear in design, meaning that if earlier program material was not of significant interest to participants, program use would discontinue.

Although some programs addressing the prevention of postpartum depression in women have succeeded in engaging fathers [23,44,45], fathers’ mental health and well-being has not been specifically targeted. Fathers are offered little support in the way of treatment or prevention of perinatal distress. Syntheses of studies investigating men’s experiences ante- and postnatally found that fathers felt overlooked in antenatal classes [46], and excluded and unsupported by maternity services in general [47]. Despite this limitation, fathers reported a desire to be actively involved in this life experience, and to be supportive of their partners [48], indicating that an opportunity to involve invested fathers is being missed. Based on qualitative interviews with new fathers, Kowlessar et al recommend that men are actively engaged, informed, and offered support [48], and that the presentation of psychoeducation material and well-being tips may help fathers feel more involved and valued during this life stage [40]. More research is required, and high quality RCTs of interventions that promote psychological well-being in both mothers and fathers are needed [49].

To date, no study has trialed a web-based intervention targeting perinatal well-being in both mothers and fathers, nor has a related cost-effectiveness analysis been conducted. This proposed study addresses these gaps, and constitutes one of few trials that focus on well-being and universal prevention, rather than the treatment of established depression. Due to this novelty, our results are likely to have wide application. Electronic programs have the potential to alleviate maternal and paternal distress, and help recent parents enjoy the enriching and exciting experience of early parenthood by increasing access to effective support at minimal cost. By addressing parents’ well-being and supporting childcare, participants may also assist in promoting positive parenting, offering potentially long-range benefits for this and future generations of Australian children.

### Trial Aims

The aim of this trial is to conduct the first RCT of a web-based intervention, *Baby Steps*, that targets perinatal well-being in both mothers and fathers (trial registration number ANZCTR12614001256662). Specifically, the first aim is to compare the effectiveness on indices of well-being using two versions of the *Baby Steps* program for first-time parents: *Babycare* (an online information-only program providing information and tips on selected childcare issues) and *Well-being* (an interactive online program including all *Babycare* content, plus parental well-being-focused content with goal-setting and problem solving tools). The second aim is to assess the cost-effectiveness of the *Well-being* program compared to the *Babycare* program.

### Hypotheses

It is predicted that participants receiving the *Well-being* program will show lower levels of distress and a higher level of quality of life at 13 and 26 weeks post-baseline, compared to participants receiving the *Babycare* program. In addition, couple relationship satisfaction, parental self-efficacy, social support, and cost-effectiveness are predicted to be greater at 13 and 26 weeks post-baseline for participants receiving the *Well-being* program, compared to participants receiving the *Babycare* program.

## Methods

### Study Design

This study is an RCT designed to evaluate the effectiveness of an online intervention targeting perinatal well-being in first-time mothers and fathers. After baseline data are collected, participating couples will be randomly allocated to receive either the *Babycare* program or the *Well-being* program. Figure 1 provides a summary of participant flow through the trial.

**Figure 1 figure1:**
[figure not shown]
Flowchart of the study design.

### Study Sample and Procedure

#### Recruitment Procedures

A total sample of 240 primiparous mother-father couples will be recruited. Participants will primarily be recruited through private and public antenatal parent education classes at the Mater Mothers’ Hospital, Brisbane, Australia. A member of the research team will visit the class immediately before the session commences to inform participants about the study and program. Couples will have the opportunity to ask questions and those interested in participating will be assisted with registration for the study. Participants will also be recruited through an exposition targeting expectant parents, and nationally through advertisements on social media and parenting forums, which will direct couples to the program website. Interested couples will be given the opportunity to ask further questions of the research team via email or telephone. During registration, all participants will be asked to select from a dropdown box regarding how they were first informed about the research trial.

